**Inclusion criteria**
• over 18 years of age
• non-specific chronic low back pain: pain in the area extending from twelfth rib to buttock fold +/- leg for > 8 weeks
• receiving exercise prescription
• ability to speak, read and write English

**Exclusion criteria**

• severe cardiovascular or metabolic disease
• inflammatory disease
• spinal tumour or fracture
• nerve root compression/compromise
• spinal cord irritation/cauda equina signs
• osteoporosis.
• Pregnancy

### Blinding

#### • Clinicians

The clinicians will be asked to agree not to disclose group allocation or questionnaire details to patients, colleagues or researchers.

#### • Patients

The plain language Explanatory Statement and Patient Consent Form will inform participants that they have an equal chance of receiving one of two acceptable exercise prescription methods.

#### • Assessor

A blinded examiner will perform all outcome assessments. Participants will be asked to refrain from discussing their treatment with the outcome assessor. At trial completion, participants will be asked to nominate whether they had been in the experimental or control group. The data manager and statistician will be unaware of treatment allocation until completion of analyses.

### Sample Size

A total of 120 patients (60 questionnaire group, 60 no questionnaire group) will be required for 80% power to detect a 5 point reduction on 100 point measure of function with 95% confidence using a two-tail test of difference between group means when raw scores have an estimated standard deviation of 10/100 points). We will allow for a 10% loss to follow-up and aim to recruit 75 participants per group. This will enable collection of data for at least 85% of enrolled participants.

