### Randomization

#### • Clinicians

Clinicians who have consented to participate will be randomly allocated, by computer-generated codes (code: exercise questionnaire group (EQ); no exercise questionnaire group (NQ)) in sealed opaque envelopes, to one of two groups with stratification to allow equal representation of qualifications. These codes will be generated by an independent researcher who has no contact with trial participants. Group 1 clinicians allocated to use the exercise preferences questionnaire will use the responses to the exercise preferences questionnaire to inform their exercise prescription. Group 2 clinicians do not use the exercise preferences questionnaire and will return the unopened envelope to a secure storage box in the reception area. These clinicians will prescribe exercise according to their usual practice.

The two groups of clinicians will not disclose their group allocation or any details or findings of the questionnaire. A code-breaker master document will be kept in a locked location at the university and cannot be viewed by reception staff or clinicians.

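### The 80% power claim treats patients as independent although clinicians are randomised; the stated 60 per group is also slightly short on its own inputs

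*Protocol article*

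**What the plan says.** The Sample Size section gives a complete calculation: "A total of 120 patients (60 questionnaire group, 60 no questionnaire group) will be required for 80% power to detect a 5 point reduction" on a 100-point function scale, "with 95% confidence using a two-tail test of difference between group means", with a raw-score SD of 10. It continues: "We will allow for a 10% loss to follow-up and aim to recruit 75 participants per group", and then "This will enable collection of data for at least 85% of enrolled participants".

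The unit of randomisation appears under Randomization, Clinicians: "Clinicians who have consented to participate will be randomly allocated, by computer-generated codes". The Abstract also says that clinicians are randomised. Methods/Design says that patients enter an arm through the clinician they are allocated to, and under Concealment only questionnaire-group clinicians open the envelope.

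Data Analysis plans patient-level comparisons: independent t tests or Mann-Whitney tests, with ANCOVA if baseline scores turn out to be related to outcome. Neither Sample Size nor Data Analysis mentions correlation within clinician, an ICC, a cluster size or a design effect.

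**The concern.** There are three separate points, of unequal weight.

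1. **Clustering (material).** The sample size formula is the one for individually randomised patients. Here the intervention is a change in how a clinician prescribes, and each clinician otherwise follows usual practice, so correlated outcomes within a clinician are plausible. If there is any such correlation, 150 patients carry less information than 150 independent ones.
2. **The stated number (minor).** The stated inputs do not lead to 60 per group.
3. **The recruitment target (minor).** 75 per group does not follow from 60 and 10% loss.

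A null result will be read against the 80% figure. If the power of a valid analysis is well below that, a non-significant comparison could be taken as evidence that the questionnaire does not help when the trial could not have settled the question.

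**Working it through.** **Inputs from Sample Size:** difference 5, SD 10 (standardised effect 0.5), two-sided 5%, 80% power, 1:1 allocation, 60 per group evaluable, 75 per group recruited, 10% loss.

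**Step 1: try to reproduce 60 per group.**
Normal approximation: n = 2 × (1.96 + 0.8416)² × (10/5)² = 62.8, so 63 per group (126 in total). Exact t test: 64 per group (128). A one-sided test would need 50, so it does not explain 60 either.

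Power for independent patients:

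| Per group | t test | Normal |
|---|---|---|
| 60 | 77.5% | 78.2% |
| 64 | 80.1% | 80.7% |
| 67.5 (75 less 10%) | 82.2% | 82.8% |
| 75 | 86.0% | 86.5% |

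**Step 2: the recruitment target.**
60/0.90 = 66.7, so 67 per group would cover 10% loss from 60. The plan recruits 75. From 75, 10% loss leaves 67.5, which is 90% retained and satisfies a floor of 85%. With the corrected number, 64/0.90 = 71.1, so 72 per group, which fits within 75.

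**Step 3: clustering.**
The documents give no number of clinicians k and no ICC. *Assumed for illustration:* k from 8 to 30, split equally between arms with equal numbers of patients; ICC 0.01 to 0.10.

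With N analysed, m = N/k patients per clinician, design effect = 1 + (m − 1) × ICC, and effective n per arm = (N/2)/design effect. Power is from a t test on k − 2 degrees of freedom with noncentrality 0.5 × √(effective n/2).

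Worked case, N = 135 (150 less 10%), k = 12, ICC 0.05: m = 11.25; design effect = 1 + 10.25 × 0.05 = 1.5125; effective n = 67.5/1.5125 = 44.6 per arm; power 57% (66% by normal approximation).

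| Analysed | Clinicians | ICC | Design effect | Effective n per arm | Power (t, k − 2 df) | Power (normal) |
|---|---|---|---|---|---|---|
| 135 | 8 | 0.10 | 2.59 | 26.1 | 33% | 44% |
| 135 | 12 | 0.05 | 1.51 | 44.6 | 57% | 66% |
| 135 | 30 | 0.01 | 1.035 | 65.2 | 79% | 82% |
| 150 | 30 | 0.01 | 1.04 | 72.1 | 83% | 85% |

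**Step 4: the patient-level t test that is planned.**
Ignoring a design effect of 1.5125 makes the standard error too small by a factor √1.5125 = 1.23. The two-sided error rate is then about 2 × [1 − Φ(1.96/1.23)] = 11% in place of 5%. Any power quoted for that test is therefore not power at the 5% level.

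**The case against.** The strongest reply is that the trial does not plan to stop at 120. It recruits 150, and with 10% loss and independent patients it has 82.2% power. Data Analysis also replaces missing scores, so the analysed set could be nearer 150. This stands as far as the arithmetic slip goes. A reader might infer from the 77.5% that the trial is underpowered through that slip; the recruitment target rules this out. (Carrying scores forward adds no real information, so 150 analysed is a generous basis.)

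A reader might also infer that the attrition figures contradict each other: 10% stated, 15% from the retention sentence, 20% from 75 down to 60. The text does not support that. The retention figure is a floor that 10% loss satisfies, and the 20% is a back-calculation that the plan never states. What remains is an unexplained margin in the safe direction.

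On clustering, the reply is that the figures rest on invented inputs and on a test that the plan does not specify. That is fair as to size. It would be wrong to say that this trial's power is 57%, or that it lies below 80% under every assumption: with 150 analysed, 30 clinicians and ICC 0.01, the same method gives 83%. It is also true that the planned patient-level test would reject more often than the cluster-level figures suggest, but it does so by exceeding the 5% error rate, so this does not rescue the 80% claim. Baseline adjustment could recover some power. With an assumed baseline correlation of 0.3, 60 independent patients per group would give about 82% by normal approximation. But ANCOVA is conditional in Data Analysis, and the stated calculation uses raw scores.

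Nor can this be left to an unseen analysis plan. The article publishes a finished power statement, and that statement does not match the randomisation it describes.

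**Conclusion.** The point holds in this form. The 80% figure is calculated for a design with independently allocated patients, which this is not. The direction is certain: any positive ICC lowers the power of a valid analysis. The size cannot be determined from the documents. Over the assumed range with 135 analysed it runs from 33% to 79% with the cluster-level t test; by normal approximation the most favourable corner just passes 80%.

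The 60 per group is an arithmetic slip of 3 to 4 patients per group, absorbed by recruiting 75 if patients are independent. The step from 60 to 75 is unexplained but harmless.

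**What to change.** Rewrite the Sample Size paragraph without changing recruitment:

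- State that 64 evaluable patients per group (128 in total) are needed for 80% power before clustering, and that 72 per group would cover the stated 10% loss, so 75 per group leaves a small margin. The 10% figure can stay.
- State the planned number of clinicians, the expected patients per clinician m, the assumed ICC and the design effect 1 + (m − 1) × ICC.
- Give the power that 150 recruits provide in a short table over ICC 0.01 to 0.10, for an analysis that accounts for clinician, and name that analysis so that it agrees with Data Analysis.
- Show any gain from baseline adjustment on a separate line, with the assumed correlation.

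The cost is one rewritten paragraph and a matching line in Data Analysis, with no extra patients. The downside is that the published power will probably look less favourable. The rewording repairs no power; it makes the claim correct for the design, so that a null result is read against the right figure.

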### Outcome measures

Socio-demographic data including age, back pain history and occupation status, will be collected at baseline. The following outcomes will be assessed at baseline, at completion of the 6 week intervention and at 12, 26 and 52 weeks: Functional ability: Oswestry Disability Index (ODI) [28], Pain: Tagged Numeric Pain Scale (NPS) [29], Fear avoidance: Fear Avoidance Beliefs Questionnaire (FABQ) [30]. The Exercise Preferences Questionnaire will be completed at baseline only and the Exercise Diary will be completed after each exercise session during the intervention and follow-up period. Time to complete the Exercise Preferences Questionnaire will be evaluated by asking the participant to note the time taken on page two of this form. Follow-up reminders will be given by phone or SMS and completed outcome measures returned by pre-paid envelope or SMS.

### Adverse effects or events

No adverse events are anticipated but will be documented by type, length of time and frequency should they occur.

### Data Analysis

Analysis will be by intention to treat. As scores are expected to improve across time, missing data will be replaced by the last score carried forward. If mean scores deteriorate across time, missing data will be replaced by the last score minus the reduction in scores anticipated using trend analysis of previous scores. Demographic characteristics and baseline data will be summarised by descriptive statistics. Distributions of all continuous data will be assessed for normality. Between-group comparisons of normally distributed data will be performed with independent t tests. Non-normally distributed data will be compared with the Mann Whitney U statistic. Relative risks and their 95% confidence intervals will be used to report group differences in proportions for similar outcomes. Continuous variables will be assessed for relationships between baseline scores and outcome. If a significant relationship is found, analysis of covariance (ANCOVA) will be conducted to test the effect of the intervention when controlling for the confounding effects of baseline scores on outcome. Effect sizes with 95% confidence intervals will be calculated for pain and function measures.

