**Methods and design:**

The study will be a randomised controlled trial comparing an exercise rehabilitation program informed by a participant preferences questionnaire compared to a program without this guideline for patients with chronic low back pain. A sample of 150 patients will be recruited in Melbourne, Australia through community-based healthcare clinics that provide supervised exercise rehabilitation programs for people with non-specific chronic low back pain. Clinicians will be randomly assigned to exercise preferences questionnaire or no questionnaire and participants will be allocated in a concealed manner. A qualitative focus group study of exercise instructor feedback about the exercise preferences instrument will be embedded in the research design. Two qualitative focus group studies will also be conducted for participants in the intervention and the control groups to obtain feedback about participants' experiences of the two types of exercise programs. The primary outcomes will be functional ability, pain, fear avoidance, exercise adherence.

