## Methods/Design

Monash University SCERH has granted approval for this study (CF08/2015 – 2008000990). The trial will be reported according to the recommendations of the CONSORT Statement [26,27] and the flow of participants through the study is represented in Figure 1. The quantitative study will compare an exercise rehabilitation program informed by a participant preferences questionnaire compared to a program without this guideline for patients with NSCLBP. The qualitative study will evaluate clinician and participant experience. Patients presenting for exercise prescription will be allocated to clinicians who either do or do not use information regarding patient exercise preferences.

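### Clinicians are randomised, but the analysis and the sample size treat patients as independent; if outcomes correlate within clinician, p-values are too small and confidence intervals too narrow

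*Protocol article*

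**What the plan says.** The randomised unit is the clinician. The abstract states: "Clinicians will be randomly assigned to exercise preferences questionnaire or no questionnaire and participants will be allocated in a concealed manner". The Randomization section agrees ("Clinicians who have consented to participate will be randomly allocated, by computer-generated codes") and adds stratification by qualification. Patients get their arm through the clinician: "Patients presenting for exercise prescription will be allocated to clinicians who either do or do not use information regarding patient exercise preferences". According to the Concealment and Randomization sections, questionnaire-group clinicians open the sealed preference form and the others return it unopened, so each clinician works in one arm only.

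The Data Analysis section then names its tests:

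- For normally distributed outcomes: "Between-group comparisons of normally distributed data will be performed with independent t tests".
- Otherwise: "Non-normally distributed data will be compared with the Mann Whitney U statistic".
- For proportions: relative risks with 95% intervals.
- If baseline and outcome prove to be related: "analysis of covariance (ANCOVA) will be conducted to test the effect of the intervention when controlling for the confounding effects of baseline scores on outcome".
- For reporting: "Effect sizes with 95% confidence intervals will be calculated for pain and function measures".

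No clinician effect, cluster-robust variance or clinician-level summary appears. The Sample Size section says "A total of 120 patients (60 questionnaire group, 60 no questionnaire group) will be required", for a difference of 5 points with a standard deviation of 10, and sets a recruitment target of 75 per group. It gives no ICC, number of clinicians or design effect.

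**The concern.** The intervention works by changing how a clinician prescribes, and the programs are otherwise each clinician's usual practice. The eligible clinicians range from physiotherapists and chiropractors to holders of certificate 4 training. Patients of one clinician share that clinician's style and skill, so their outcomes may well be correlated. Clinicians are nested within arm, so this correlation does not cancel in the comparison between arms. A standard error computed as if patients were independent leaves out the covariance between patients of the same clinician.

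This affects every between-group p-value and interval in the trial, including those for function and pain. A chance difference between the clinicians drawn into one arm and those drawn into the other could be reported as an effect of the questionnaire. Adjusting for the baseline score does not remove a clinician effect on the outcome.

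**Working it through.** **Inputs from the article.** Difference 5, standard deviation 10, two-sided 5%, 80% power, 60 per group required, 75 per group recruited, 10% loss allowed. Analysis is by intention to treat with missing scores filled in, mainly by carrying the last score forward, so about 75 per arm would be analysed.

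**Inputs assumed.** The number of clinicians per arm (k, taken as 4 to 15, with equal numbers of patients each) and the ICC (taken as 0.01 to 0.10).

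**Step 1: the plan's own sample size.** n per arm = 2 × (1.960 + 0.842)² × 10² / 5² = 62.8, so 63 per arm and 126 in total, against the stated 60 and 120. With 60 per arm the power is 78.2% by the normal formula. The stated figure is thus close to the ordinary formula for independent patients and slightly below it. It leaves no room for a design effect.

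**Step 2: what the independent t test omits.** With m = n/k patients per clinician, the variance of an arm mean is (SD²/n) × DE, where DE = 1 + (m − 1) × ICC. The patient-level test uses SD²/n. The true size of the nominal 5% test is therefore about 2 × [1 − Φ(1.960/√DE)], and the interval should be √DE times as wide.

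**Step 3: results with n = 75 per arm.**

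| Clinicians per arm | Patients per clinician | ICC | DE | True size | √DE |
|---|---|---|---|---|---|
| 15 | 5 | 0.01 | 1 + 4 × 0.01 = 1.04 | 5.5% | 1.02 |
| 10 | 7.5 | 0.05 | 1 + 6.5 × 0.05 = 1.325 | 8.9% | 1.15 |
| 6 | 12.5 | 0.05 | 1 + 11.5 × 0.05 = 1.575 | 11.8% | 1.25 |
| 4 | 18.75 | 0.10 | 1 + 17.75 × 0.10 = 2.775 | 23.9% | 1.67 |

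If only 60 per arm were analysed, the middle case (6 clinicians, ICC 0.05) has DE = 1 + 9 × 0.05 = 1.45 and a true size of 10.4%. The outer cases become 5.3% and 20.6%. Simulated t tests with 60 per arm and 5 to 30 clinicians per arm agreed with the formula within about 0.5 percentage points.

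**Step 4: small-sample degrees of freedom.** With 6 clinicians per arm there are 2 × 6 − 2 = 10 clinician-level degrees of freedom, and the t quantile is 2.228 against 1.976 on 148. The interval in the middle case should then be 1.255 × 2.228/1.976 = 1.41 times as wide.

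**Step 5: power of a valid analysis.** In the middle case the effective number per arm is 75/1.575 = 47.6. Power is Φ(0.5 × √(47.6/2) − 1.960) = 68%, or about 60% with 10 degrees of freedom. With 75 independent patients per arm it would be 86%. In the most favourable case (15 clinicians, ICC 0.01) it is about 83% with clinician-level degrees of freedom, so the loss is not universal.

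**The case against.** The strongest defence is that nothing in the article establishes the size of the problem. Inflation needs a positive ICC and more than one patient per clinician, and neither is stated. With many clinicians and a low ICC the true size stays close to 5%. This stands, and it is why the point is conditional. The upper figure of 24% needs few clinicians and a high ICC together, and should not set the priority.

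A second defence is that an article may leave analysis detail to a separate plan. That fails here, because the article names the tests, and those tests assume independence.

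A third is that the abstract speaks of concealed allocation of participants, and the Blinding section has patients told that their chances are equal. Neither describes patient-level randomisation. Even if patients were assigned at random to clinicians, clinicians would still be nested within arm.

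Four stronger readings are tempting, but the documents do not support them:

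- **Each clinician treats several trial patients.** No section says so. It is a likely inference, since one patient each would need 150 clinicians.
- **Clinician variation is wholly confounded with arm.** It is nested, not confounded. Variation among clinicians within an arm can be estimated, which is what makes a repair possible.
- **Leaving out the qualification stratum inflates the type I error.** Ignoring a stratification factor generally does not. It is a sensible covariate but not the defect.
- **Only wording needs to change, because clinician codes are already held.** The codes in the Randomization section denote the group. No section says that each patient's treating clinician is kept in the trial data.

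**Conclusion.** The concern holds in conditional form. The analysis and the sample size both ignore a level of clustering that the trial's own randomisation creates, and no section deals with it. The direction is certain if the ICC is positive and clinicians treat more than one patient each: type I error above 5% and intervals too narrow. The size cannot be fixed from the documents. Under the assumptions used (75 analysed per arm, 4 to 15 equally sized clinician groups per arm, ICC 0.01 to 0.10), the true size lies between about 5.5% and 24%. It is about 12% with 6 clinicians per arm and ICC 0.05, where the interval should be at least 25% wider before small-sample degrees of freedom are applied. Confidence is high for the direction and limited for the size. A reader might infer that the tests are certain to be badly inflated, but the documents do not go that far. The point should still be settled before analysis, because it touches every between-group result and has a standard remedy.

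**What to change.** In the Data Analysis section, replace the patient-level tests with an analysis that accounts for clinician. A linear mixed model with a random clinician intercept, baseline score and qualification stratum as covariates, and Kenward-Roger or Satterthwaite degrees of freedom would do. If there are few clinicians per arm, compare clinician-level means instead. Use a cluster-adjusted method for the relative risks. Terms for repeated visits are not needed to repair this defect.

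Also:

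- Record the treating clinician's code for each patient, and confirm that it reaches the analysis dataset without breaking the analyst's blinding to arm.
- Report the ICC for each main outcome, and describe the trial as cluster-randomised by clinician.
- Restate the power in the Sample Size section under a stated ICC and number of clinicians.

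The analysis change itself needs no new patients or staff. It costs one extra variable if clinician is not already captured, and wider intervals. The stated power also falls below 80% under many plausible ICCs: about 60% to 68% with 75 analysed per arm, 6 clinicians per arm and ICC 0.05. Spreading the same patients over more clinicians would reduce that loss.

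### Baseline adjustment hangs on a significance pre-test, and the plan does not say whether ANCOVA replaces or accompanies the unadjusted test

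*Protocol article*

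**What the plan says.** The Data Analysis section sets out two choices that are made from the trial's own data.

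- **Choice of unadjusted test.** Continuous data are checked for normality, by no stated criterion. Data that pass go to an independent t test. For the rest, "Non-normally distributed data will be compared with the Mann Whitney U statistic".
- **Choice to adjust.** Baseline scores are examined for a relationship with outcome. "If a significant relationship is found, analysis of covariance (ANCOVA) will be conducted to test the effect of the intervention", and the stated reason is to control confounding by the baseline score.

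The section does not say which result counts when both an unadjusted test and an ANCOVA have been run. Nor does it say what happens when data are non-normal and baseline also predicts outcome.

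The abstract lists several primary outcomes: "The primary outcomes will be functional ability, pain, fear avoidance, exercise adherence". Under Outcome measures, the first three are scored by ODI, NPS and FABQ, each taken at baseline and at four follow-up times. The Sample Size section rests on an unadjusted comparison: "80% power to detect a 5 point reduction on 100 point measure of function with 95% confidence using a two-tail test", where "raw scores have an estimated standard deviation of 10/100 points".

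**The concern.** In a randomised trial, the reasons to adjust for baseline are precision and chance imbalance. Both follow from the expected correlation between baseline and outcome, which can be judged in advance. Neither depends on a significance test in the trial data, and randomisation removes the systematic confounding that the plan gives as its reason.

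The larger difficulty is that the sentences on the t test and Mann-Whitney are unconditional, while the ANCOVA sentence adds a further test of the same treatment effect. A reader cannot tell which p-value is the result. Three scales at four follow-up times give 3 × 4 = 12 comparisons. The two choices could fall differently in each, so the report could mix adjusted means, unadjusted means and rank comparisons.

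At stake is either power, if the unadjusted result is the headline, or the false-positive rate, if the more favourable of two results can be claimed.

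**Working it through.** **Inputs from the Sample Size section.** Difference 5 points, SD 10, two-sided 5% level, and "60 questionnaire group, 60 no questionnaire group". **Assumed.** The baseline-outcome correlation r, which the article does not give, is taken at 0.2 to 0.7. Patients are treated as independent.

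**Step 1: the plan's own figure.** n per arm = 2(1.960 + 0.842)² × 10²/5² = 62.8, so 63 per arm (126 in total). The exact t test needs 64 per arm (128). The stated 120 is slightly short: at 60 per arm, power is 78.2% by the normal approximation and 77.5% by the exact t test. The gap is small and does not drive this point.

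**Step 2: unadjusted test as headline, against always ANCOVA.** ANCOVA reduces the SD to 10√(1 − r²), so the standardised difference becomes 0.5/√(1 − r²). Power at 60 per arm (exact t):

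| r | SD after adjustment | Standardised difference | ANCOVA | Unadjusted t |
|---|---|---|---|---|
| 0.3 | 9.54 | 0.524 | 81.3% | 77.5% |
| 0.5 | 8.66 | 0.577 | 88.0% | 77.5% |
| 0.7 | 7.14 | 0.700 | 96.7% | 77.5% |

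The loss is about 4, 10 and 19 power points.

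**Step 3: ANCOVA replaces the t test when the pre-test is significant.** This was simulated with 60 per arm, normal data and 10,000 runs per setting.

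| r | Pre-test triggers ANCOVA | Power, two-stage rule | Power, always ANCOVA |
|---|---|---|---|
| 0.2 | about 58% | 78.6% | 78.9% |
| 0.3 | about 90% | 80.7% | 80.8% |
| 0.5 | about 100% | 87.85% | 87.85% |

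A second simulation gave 77.7% against 78.3% at r = 0.2, and 87.8% for both at r = 0.5. The loss is therefore under about 1 point. Type I error of the two-stage rule was 4.7% to 5.2% across settings. The reason is simple: when r is large enough for adjustment to matter, 120 patients nearly always give a significant pre-test.

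**Step 4: either test may be claimed.** Under no effect, the two test statistics are approximately bivariate normal with correlation √(1 − r²). The chance that at least one exceeds 1.96 in absolute value is:

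- r = 0.3 (correlation 0.954): 6.4%
- r = 0.5 (correlation 0.866): 7.3% to 7.4%
- r = 0.7 (correlation 0.714): 8.3%

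Direct simulation gave 6.5%, 7.4% and 8.5%.

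**Step 5: the normality check.** Assume a Shapiro-Wilk test at 5% in each arm. Truly normal data then go to Mann-Whitney in about 1 − 0.95² = 9.75% of trials (simulated: 9% to 10%), and power changes by only about 1 point. For clearly skewed data (gamma, shape 2, pure shift), Mann-Whitney has about 89% to 90% power. The t test has about 78%. ANCOVA has about 81% at r = 0.3, 86% at r = 0.5 and 96% at r = 0.7.

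**The case against.** The strongest reply is that the section describes a sequence in which ANCOVA supersedes the unadjusted test once triggered. Step 3 shows that such a rule costs almost nothing. Chance imbalance does little harm under it either, because imbalance matters only when baseline predicts outcome, and that is when ANCOVA is triggered. An analysis plan that is not shown may also say which result is primary, and the Assessor paragraph under Blinding keeps the statistician blind until the analyses are complete.

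Much of this stands. A reader might infer that the pre-test in itself wastes precision or inflates type I error. The text does not support that, because both harms need a further rule that it does not state. Three other inferences also go too far:

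- **Few clinicians, so serious baseline imbalance.** The article gives no number of clinicians.
- **Mann-Whitney is simply the worse test.** With skewed data it can beat both the t test and ANCOVA. Its limitation is that it uses no baseline score and gives no mean difference to set against the 5-point target. The section does promise effect sizes with intervals for pain and function, on an unstated scale.
- **Failing to adjust for the qualification stratum is an error.** Clinicians are randomised "to one of two groups with stratification to allow equal representation of qualifications", but silence on this covariate is the kind of detail a condensed article leaves out.

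The reply does not remove the point. The article states a data-dependent rule for adjustment without saying how its result ranks against the unadjusted test. The sequential reading is possible but unwritten, and the sample size calculation fits an unadjusted headline equally well. Blinding to arm labels does not hide two p-values or say which is primary.

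**Conclusion.** The point holds as a fault of prespecification whose cost depends on an unstated rule. If ANCOVA replaces the unadjusted test when triggered, the cost is under about 1 power point and type I error is about 5%. If the unadjusted test is the headline, power is about 77.5% instead of about 81%, 88% or 97% at r = 0.3, 0.5 or 0.7. If either result may be claimed, type I error is about 6% to 8%.

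These figures rest on the plan's 5-point difference and SD of 10, 60 patients per arm, normal data, assumed values of r and independent patients. Because clinicians are the unit randomised, clustering would lower every power figure. That is a separate matter. The change is worth making because it closes all three readings at almost no cost.

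**What to change.** For ODI, NPS and FABQ, name one primary analysis: the follow-up score compared between groups with adjustment for its own baseline score, in all cases. Delete the significance pre-test and the reference to confounding. Report the unadjusted t test or Mann-Whitney only as a sensitivity analysis, which keeps a rank-based check if scores prove skewed. Adjusting for the qualification stratum used in randomisation is a reasonable secondary addition. Exercise adherence comes from a diary kept during the intervention and follow-up, with no baseline score described, so this change does not extend to it.

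The cost is a few lines of wording. The three baseline scores are already collected, and no change to sample size or data collection is needed.
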